**Fig. 4 Fig4:**

A pictorial representation of a theoretical trial from the Mental Number Line Bisection task. The participant is asked to indicate the midpoint number between the numbers 54 and 70, which are verbally presented by the experimenter. A negative bias score indicates that the centre of the participant’s mental number line is shifted towards larger numbers, consistent with an under-representation of the left side of space relative to the right side of space

***Spatially-defined motor function*** We use the Directional Hypokinesia task to assess two distinct forms of motor neglect – directional hypokinesia, i.e. relative slowing in the initiation of movements directed toward the affected side, and directional bradykinesia, i.e. relative slowing in the execution of movements directed toward the affected side of space [103]. The task measures movement initiation and execution times to targets that appear on the left or the right side of the screen. The task follows the exact procedure previously used for research with hemispatial neglect patients [57]. A black 1.4° fixation cross and two black 3° × 3° squares, one 12° to the left and one 12° to the right of the fixation cross, are on constant display (locations are re-expressed as affected and unaffected Visual Field, VF). Each trial is initiated by the participant pressing and holding a button with their index finger. After a time interval that varies randomly between 1500 ms and 3000 ms a black target (1.4° high “X”) appears inside one of the squares, in a pseudorandomized order, for 2000 ms. The target onset initiates the response window and the participant is required to release the button, touch the screen in the location where the target appeared, and then return their index finger to the button as fast as possible, which initiates the next trial. There are 30 trials per block. A touch screen is used to monitor the accuracy of pointing-to-target movements. The Reaction Times (RTs) to release the button after the target onset (Movement Initiation Time, MIT) are recorded, as well as time taken between releasing the button and touching the screen (Movement Execution Time, MET). There are three different hand Starting Positions (location of the button box): 25 cm to the left from body midline, central (aligned with the body midline), and 25 cm to the right from body midline (the locations are re-expressed as the affected, central, and unaffected side). Manipulating the hand Starting Position allows dissociation between perceptual component of the task (e.g., slower detection of the targets on the affected side) and the true directional hypokinesia. Participants perform each condition once with each hand in separate blocks, giving a total of 6 conditions (unaffected hand from the unaffected side, unaffected hand from the centre, unaffected hand from the affected side, affected hand from the unaffected side, affected hand from the centre, affected hand from the affected side). The order of the Starting Positions is counterbalanced between participants, with the only restriction that they alternate between the unaffected and the affected hand in each subsequent block to reduce fatigue.

We will calculate mean MITs and METs for each combination of VF in which the target appeared (affected and unaffected) and hand Starting Position (affected, central, and unaffected location), separately for each hand used to complete the task. Directional hypokinesia would be indicated by slower initiation of movements (MIT) towards the affected side of space, independent of which arm is used [57, 103, 104]. Directional bradykinesia would be indicated by slower movement execution times (MET) towards targets appearing in their affected side of space, even when using the unaffected arm.

To dissociate any signs of directional hypokinesia from potential mechanical constraints, two indices of directional hypokinesia will be derived based on the analyses described in previous research [57]. Movement pathways and indices are illustrated in Fig. 5. The first index (A) quantifies the difference in MITs to the targets in the affected vs. unaffected VF as a function of the direction of the movements, i.e,. reaching toward the affected side (from central Starting Position) relative to reaching toward the unaffected side (from affected Starting Position). Index A will be calculated as: [central Starting Position (MIT affected VF – MIT unaffected VF) – affected Starting Position (MIT affected VF – MIT unaffected VF)]. Thus, a larger value on this index will indicate greater directional hypokinesia. A potential drawback of Index A is that it involves planning a movement across body midline (from the affected Starting Position to the unaffected VF) that covers a longer distance and may be more difficult than other movement trajectories. Therefore, we will also derive a second index (B) that directly quantifies the relative slowing in the ability to initiate movements to the targets in the affected VF when making movements of the same physical length toward the affected side (from central Starting Position), versus toward the unaffected side (from affected Starting Position). Index B will be calculated as [central Starting Position (MIT affected VF) – affected Starting Position (MIT affected VF)]. Positive values on each index (A and B) would indicate hypokinesia for the affected side. Analogous indices A and B will be calculated for METs, and positive values of each index would indicate directional bradykinesia for the affected side.

**Fig. 5 Fig5:**
[figure not shown]
Indices of Directional Hypokinesia task. Target locations (affected and unaffected Visual Field, VF) and hand Starting Positions (affected, central, and unaffected) are presented as an example of a participant with CRPS of left arm. Index A is calculated as initiation time of the movements represented by arrows [(1–2) – (3–4)]. Index B is calculated as initiation time of movements (1–3)

***Body representation*** As an objective measure of body representation we use a modified Hand Laterality Recognition task based on a procedure described elsewhere [58]. The stimulus set was developed specifically for the current study (examples shown in Fig. 6) and the final images were chosen based on the results of a pilot study reported in Additional file 2. The images depict gender-neutral right and left (mirror-reversed) hands in different postures and are presented at four different orientations (0°, 90°, 180° and 270°). In each trail, a black 0.1° fixation cross on a white background is on constant display. After 1000 ms a colour image of a hand (12.9° × 12.9°) is randomly presented 8° to the left or to the right of the fixation cross (i.e., in the left or the right VF, as in a previously published similar procedure [7]) for 180 ms. This period is short enough to prevent foveation of the stimuli, ensuring that the images are presented to one visual hemifield. The participants are required to indicate whether the image represented the right or the left hand by pressing the red or green button using the index and middle fingers of their unaffected hand. Speed and accuracy are both emphasised but there is no upper time limit for the response, and the button press initiates the next trial. Prior to the main task, participants complete a practice block of 12 trials (with 2000 ms stimulus presentation times) that includes feedback, until they reach at least 75% accuracy across the entire practice block. They repeat the practice to ensure that they are able to perform the task above chance level. In the main task, there is a total of 100 trials (25 images × 2 hemifields × 2 depicted hands) conducted in a single block. Accuracy rates and RTs of the correct responses are calculated separately for the images of hands corresponding to the participant’s affected and unaffected limbs, and for the VFs corresponding to their affected and unaffected side of space (matched sides in healthy controls). As the task requires mental rotation of the images of hands, slower RTs and lower accuracy rates are considered to be an indicator of a distorted representation of the depicted limb [7, 58, 105]. To obtain single Hand Laterality Recognition indices, we will also calculate the differences in accuracy rates and RTs between depicted affected and unaffected hands. Positive accuracy index (unaffected – affected) and positive RT index (affected – unaffected) would indicate distorted representation of the affected limb.

**Fig. 6 Fig6:**
[figure not shown]
Example stimuli in the Hand Laterality Recognition task. Images of hands in four postures and rotation angles were included in the task

### Blinding

All outcome measurements are recorded by a researcher who is blind to group allocations (MH). A researcher ([name]) who is not involved in data collection allocates participants with CRPS to treatment groups 1–5 days before RS2. [name] or another researcher not involved in data collection ([name]) trains the participants in how to carry out the PA treatment or sham treatment in a self-guided manner at the end of RS2. The participants return the goggles in sealed opaque bags after completing the treatment in RS3 so that the primary researcher (MH) remains blind to their treatment allocation. MH will be unblinded as to the group allocations of the participants once the last person has completed RS4, as there will be no further research sessions in which she will assess symptoms. Follow-up measurements in weeks 19 (LTFU1) and 31 (LTFU2) will be carried out via postal questionnaires scored by research assistants who are blind to the group allocations.

The participants will be blind to their group allocations as they are not made aware of the specific nature of the intervention beyond that it involves sensory-motor coordination, nor the type of goggles used in the other treatment arm. In the information sheet and the training materials, the same terms are used to describe both treatment arms. For instance, all participants will be informed that sensory-motor training involves reaching out to targets with their affected arm while wearing glasses fitted with lenses that distort vision. For ethical reasons, participants have to be told that they might receive either real or control treatment, and the meaning of double-blind randomised control trial will be explained to them in the information sheet and during training in how to carry out the treatment. A more general term “sensory-motor adaptation” is used to refer to PA in all study documents and instructions that the participants receive, to reduce the possibility that they could determine their treatment condition based on descriptions of PA on the Internet. At the end of the last in-person session (RS4) they will also be asked whether they have a belief about which condition they were allocated to, and their degree of confidence about this belief. They will be unblinded once data collection for this study is completed for all participants. Also, a participant might be unblinded before this time should they experience any worsening of symptoms that causes them concerns. If so, that participant will be withdrawn from the study in that no further data will be collected from them.

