In the event of the participant’s withdrawal from the study, their data from any completed research sessions will be included in the analysis as far as possible. Participants who withdraw after RS2 will be considered lost to follow-up. For any participant who withdraws before RS4, an additional participant will be recruited to the trial such that there will be 42 full datasets for RS1-RS4. This strategy is implemented to assure sufficient and similar number of participants in each treatment arm. To address any potential selection bias, we will use intention to treat as our primary analysis, and per-protocol as supportive analysis (see “Treatment outcome analyses” section). Should participants deviate from the intervention protocol (e.g., missed treatment sessions), the number of logged treatment sessions can be used as a possible covariate in the final analyses.

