Criteria for discontinuing the allocated treatment before the 2 weeks have elapsed are a participant’s withdrawal from the study, or reports of experiencing an increase in CRPS symptoms that significantly heightens their discomfort or distress. As the treatment procedures require repeated movements of the CRPS-affected arm, participants may experience pain related to movement. However, this is expected to be temporary and no greater than the pain that could accompany standard physiotherapy or daily activities. To date, there have been no publications reporting serious adverse events related to PA in healthy controls or clinical populations (patients with stroke, Parkinson’s disease [41], or CRPS). In one case study exploring the effects of different PA directions and strengths, one CRPS patient experienced a small, temporary increase in pain when they performed PA using optical deviation towards the affected side [24]. Similar events in the current study are highly unlikely, as all PA is conducted with optical deviation away from the CRPS-affected side, i.e., in the direction thought to achieve therapeutic effects. Each participant is assigned their own dedicated set of prism goggles in a bag labelled with their participant code. The direction of optical deviation is independently checked by two people before the goggles are placed in a labelled bag. Any unexpected serious adverse events related to the administration of any study procedures will be reported to the researcher responsible for blinding ([name]) who will then make any decisions about discontinuing an individual’s participation and/or the trial, in consultation with the protocols for dealing with adverse events as outlined by the Research Ethics Committees.

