#### Primary outcomes

A change between RS2 (immediately before the commencement of treatment) and RS3 (immediately after the end of the treatment period) in current self-reported pain intensity and CRPS severity score [35, 52] are the primary outcomes. People with CRPS consider pain relief to be the highest priority for recovery [59], and pain intensity is the most common primary outcome in chronic pain trials [60]. Current pain intensity is measured using item 6 of the Brief Pain Inventory (BPI; short form) [42], which is a Numerical Rating Scale (NRS) ranging from 0 – “no pain” to 10 – “pain as bad as you can imagine”. The BPI has high reliability [42]. In addition to pain, CRPS involves a range of other debilitating symptoms, some of which were also affected by PA in previous studies [22, 24]. Therefore, we included a comprehensive measure of symptoms severity as the second primary outcome. The CRPS severity score assessment protocol follows the 16-points scoring system published by Harden and colleagues [35]. This continuous index of CRPS symptom severity has good discrimination abilities, concurrent validity and adequate sensitivity to change [35, 52], and has been recommended as one of the core outcome measures for CRPS clinical studies [61].

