#### Treatment outcome analyses

We will conduct intention to treat (ITT) as our primary analysis to examine the overall effects of prism adaptation. The ITT analysis will include all allocated participants with CRPS regardless of treatment adherence and completion of outcome measurements. Baseline post-randomisation observation (RS2) carried forward will be used to account for missing data in ITT analysis, as the participants are expected to return to pre-treatment baseline over time. The exception is the Patient Global Impression of Change questionnaire that is only completed in the post-treatment research sessions, in which case the RS3 observation will be carried forward. Missing data from the computer-based tasks within each research session will be replaced by group mean for the particular task condition (with an exception of Directional Hypokinesia task, where some participant with CRPS may not be able to complete the task using the affected limb; in such cases only the conditions completed with the unaffected limb will be analysed). Missing daily logbook ratings will be interpolated using linear regression.

We will also conduct a supportive per-protocol (PP) analysis to see whether PA treatment can benefit the participants with CRPS who were able to perform it according to the trained protocol compared to those participants who were able to complete the sham treatment according to trained protocol [111]. The PP population will be the subset of the ITT population who provided complete outcome data for RS1-RS4 (i.e. attended all in-person research sessions and completed the primary outcome measures) and missed no more than 6 treatment sessions.

We will use confidence intervals to compare the RS1 primary outcomes scores of the participants with CRPS who withdrew and those who remained in the trial until RS4 to assess any potential selection bias. The timing and reasons for withdrawal will be presented in a CONSORT diagram.

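### A participant unblinded because symptoms worsened is no longer measured, and the primary analysis then fills the missing outcome with the pre-treatment value, so a bad outcome is recorded as no change

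*Protocol article*

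**What the plan says.** Two rules meet here.

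- **Blinding:** "a participant might be unblinded before this time should they experience any worsening of symptoms that causes them concerns". When that happens, "that participant will be withdrawn from the study in that no further data will be collected from them".
- **Treatment outcome analyses:** "The ITT analysis will include all allocated participants with CRPS regardless of treatment adherence and completion of outcome measurements". For the gaps, "Baseline post-randomisation observation (RS2) carried forward will be used to account for missing data in ITT analysis", and the reason given is "as the participants are expected to return to pre-treatment baseline over time".

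The Primary outcomes section defines both primary outcomes, current pain and the CRPS severity score, as the change from RS2 to RS3. The RQ1 analysis section fits a six-time-point ANOVA to pain (RS1 to LTFU2) and a four-time-point ANOVA to the severity score (RS1 to RS4).

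Three other passages bear on the point. The Treatment section lists "reports of experiencing an increase in CRPS symptoms that significantly heightens their discomfort or distress" as a ground for stopping the allocated treatment, separately from study withdrawal. The Recruitment and participant retention section keeps data from sessions already completed. It also states: "For any participant who withdraws before RS4, an additional participant will be recruited to the trial".

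**The concern.** For this group the trial's own rule creates the missing data, and the trigger is the outcome under study. A participant who gets worse and is unblinded has no later measurement, and the analysis writes in the pre-treatment value.

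The stated reason for carrying RS2 forward is an expected return to baseline over time. That does not fit RS3, which the Design section places on the day after the last treatment session. Nor does it fit someone unblinded because they had moved away from baseline in the harmful direction.

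At stake is the between-arm comparison of mean change. If one arm has more of these cases, its mean looks better than it was, and the comparison is least able to show harm where harm occurred.

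**Working it through.** **1. The plan's own figure.** Inputs from Sample size and power calculation: difference 2 points, SD 1.98, type I error 5%, power 90%. The two-sided normal approximation gives n per arm = 2 × (1.960 + 1.282)² × 1.98² / 2² = 20.6, so 21 per arm and 42 in total, as stated. Up to 52 are to be enrolled, or 26 per arm. The 2-point target and 26 per arm are used below.

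**2. What the rules do, by time of unblinding.**

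| Unblinded for worsening | RS3 | RS4, and LTFU1-2 for pain | Effect |
|---|---|---|---|
| Before RS3 | Set to RS2 | Set to RS2 | RS2 to RS3 change is exactly 0 |
| After RS3 | Observed value kept | Missing later visits set to RS2 | Primary contrast intact; later points in the primary ANOVAs show a return to baseline that nobody measured |
| Worsens, not unblinded | Still measured | Still measured | None from this rule |

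**3. Whether another stated analysis recovers the worsening.**

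- The per-protocol set needs complete RS1 to RS4 data, so it omits these participants.
- The check on withdrawals compares RS1 scores, which precede treatment.
- The NNT counts responders. A worsened participant is a non-responder either way, so the NNT is neither distorted nor informative here.
- Recruiting an additional participant does not remove the first one from the intention-to-treat set, where the change remains zero.

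**4. Size.** If k of N participants in an arm worsen by w points before RS3 and are set to zero, the arm's mean change is too favourable by k × w / N. The protocol gives neither k nor w, so both are assumptions, with no such cases in the other arm. With N = 26:

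| k | w = 2 | w = 3 | w = 4 |
|---|---|---|---|
| 1 | 0.08 | 0.12 | 0.15 |
| 2 | 0.15 | 0.23 | 0.31 |
| 3 | 0.23 | 0.35 | 0.46 |
| 4 | 0.31 | 0.46 | 0.62 |

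For w = 3 the range is 0.12 to 0.46 points, or 6% to 23% of the 2-point target. The formula holds equally for the severity score, with w in that score's points.

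**5. Dependence on imbalance.** This was simulated with 20,000 runs, a two-sample t-test, change SD 1.98, no true mean difference, and 21 or 26 per arm.

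- Everyone in one arm who worsens by at least 3 points (6.5%) is reset to zero, and nobody in the other: apparent benefit 0.25 points, rejection rate 7% to 8%.
- Same, with a 2-point trigger (about 16% of the arm): about 0.47 points, 13% to 16%.
- The rule applied equally in both arms, for triggers of 2, 3 and 4 points: bias within 0.01 points, rejection rate about 5%.

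The first two cases are one-sided extremes.

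**The case against.** The path is narrow. Unblinding is only a possibility, and data collection ends only if it happens. Stopping treatment because symptoms increased does not by itself bar anyone from RS3. An RS3 value already recorded is kept. The primary contrast is therefore exposed only to unblinding between RS2 and RS3, about two weeks. The Treatment section regards a pain increase like the one reported with the opposite prism direction as highly unlikely, and the arm movement that may cause temporary pain is common to both arms. All of this stands and limits the reach. It does not remove the mechanism.

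Four stronger readings are tempting and are not supported.

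- *Worsening vanishes from the trial's record.* It does not. Timing and reasons for withdrawal go into the CONSORT diagram, and daily logbook ratings made before withdrawal are compared by group. What is lost is the worsening in the primary outcomes.
- *The analysis is not intention to treat.* All allocated participants are kept. The problem is the value entered for some of them.
- *Carrying RS2 forward cuts power to 86%.* That needs the whole 20% drop-out to fall between allocation and RS3. The 20% refers to complete RS1 to RS4 datasets, so it can include losses before allocation or after RS3. With 26 per arm, power is about 91% if 10% miss RS3 and 93% if 5% do, both above the planned 90%.
- *A mixed model or multiple imputation under missing at random would cure it.* Suppose 3 of 26 worsen by 3 and the other 23 improve by 2. The true mean change is (−46 + 9)/26 = −1.42. Carried forward gives −46/26 = −1.77, an error of 0.35. The observed-data mean, which such methods in effect assign, is −2.00, an error of 0.58. The bias grows.

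Pain ratings given after unblinding are subjective, so stopping collection has some rationale. Flagging them meets that better than replacing them with zero change.

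**Conclusion.** The point holds in this limited form. For a participant unblinded because of worsening, the two rules together replace a bad outcome with a neutral one: in the primary contrast if unblinding precedes RS3, and at the later time points of the primary ANOVAs if it follows. The stated justification does not cover these cases, and none of the other stated checks on the primary outcomes recovers them.

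The direction depends on which arm has more such cases. The documents do not show that prism adaptation would be that arm, so a reader should not infer a built-in bias in its favour. The size rests on assumed counts: 0.12 to 0.46 points for 1 to 4 of 26 in one arm worsening by 3 points, and close to nil if the arms are equal. The mechanism is certain from the text; its practical size is not known. No later analysis plan can recover an RS3 value that was never collected, so the point belongs in the protocol.

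**What to change.** Amend the Blinding section so that unblinding does not by itself end data collection. These participants would still be asked to attend RS3 and RS4 and to return the postal questionnaires unless they withdraw consent. Flag what is collected after unblinding and include it in the intention-to-treat analysis. Leave the criteria for unblinding and for stopping treatment unchanged.

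Under Treatment outcome analyses, add one sensitivity analysis: where a participant unblinded for worsening still has a missing outcome, assign an unfavourable value instead of RS2. Replacing carried-forward values by a missing-at-random method is not part of this fix, because it does not correct this bias.

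The cost is a short amendment, a few extra visits or questionnaires, and some self-reported outcomes given with knowledge of the allocation. The article describes recruitment as ongoing, so the change could still apply to participants yet to be followed up.
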